# Efficacy and safety of early YAG laser vitreolysis for symptomatic vitreous floaters: the study protocol for a randomized clinical trial

**DOI:** 10.1186/s13063-024-07924-1

**Published:** 2024-01-13

**Keywords:** Vitreous floaters, Vitreolysis, Nd: YAG laser

## Abstract

**Background:**

Vitreous floaters are a common ocular condition that affects individuals of all ages. Although vitreous floaters are typically benign, they can significantly impair visual acuity and quality of life. Laser vitreolysis, which uses an Nd: YAG laser to vaporize collagenous vitreous opacities, is increasingly being used as a treatment option. However, there is currently a lack of evidence regarding its efficacy and the appropriate timing of its application. This study aims to evaluate the efficacy and safety of early intervention with YAG laser vitreolysis in treating symptomatic vitreous floaters.

**Methods:**

The present study is a randomized, controlled, double-blind clinical trial. A total of 70 participants with symptomatic floaters for 1 month were prospectively recruited. These participants will be randomly assigned to two groups, with 35 individuals in each group: the early treatment group and the delayed treatment group. Participants assigned to the early treatment group will undergo YAG laser vitreolysis immediately, followed by a sham laser treatment 3 months later. On the other hand, participants assigned to the delayed treatment group will receive a sham laser treatment and then undergo YAG laser vitreolysis 3 months later. The follow-up time points will be 1, 3, 6, and 12 months from randomization. Primary outcomes will be participants’ self-reported improvement in visual disturbance on a scale of 1 to 10 and their scores on the National Eye Institute Visual Functioning Questionnaire 25 (NEI VFQ-25). Secondary outcomes will be an objective evaluation of the effectiveness of the treatment in reducing vitreous floaters through OCT and fundus photography and tracking any adverse events related to the eyes or overall health.

**Discussion:**

This clinical trial aims to evaluate the effectiveness of YAG laser vitreolysis in treating symptomatic vitreous floaters and assess the safety of performing early intervention with YAG laser vitreolysis.

**Trial registration:**

ClinicalTrials.gov NCT05800353. Registered on 10 March 2023.

**Supplementary Information:**

The online version contains supplementary material available at 10.1186/s13063-024-07924-1.

## Background

Floaters are visual disturbances that occur when the vitreous in the eye becomes cloudy, which can happen when the posterior vitreous detaches. Vitreous floaters can cause serious visual discomfort symptoms [1, 2]. In an electronic survey that recruited 603 smartphone users, 76% of the participants reported seeing floaters, while 33% complained of noticeable visual impairment because of them [3]. In the past, observation and vitrectomy were the main methods for treating vitreous floaters. Although the majority of vitreous floaters patients are currently recommended for clinical observation, many still cannot tolerate the related visual symptoms and seek further treatment. Vitrectomy has a definite therapeutic effect, but as an invasive procedure, it has relatively more complications and higher costs and is still not accepted by most clinical practitioners [4]. In recent years, ND: YAG laser vitreolysis has gained popularity as a fast, relatively inexpensive, and less invasive method for treating vitreous opacities and is increasingly being considered a viable option for managing vitreous floaters [5].

In 2002, Delaney et al. [6] applied YAG laser to treat 38 patients with vitreous floaters, and the results showed that 38% of patients experienced a moderate or greater subjective improvement in symptoms. Among them, 11 patients were unsatisfied with the outcome of the YAG laser and subsequently underwent vitrectomy. In 2017, Shah et al. [7] conducted the first randomized controlled trial comparing YAG laser and sham laser treatment for vitreous floaters. The results showed that 53% of patients in the true laser group had a significant subjective improvement in symptoms, while there was no significant improvement in the sham laser group. There were no significant differences in adverse reactions between the two groups, further confirming the effectiveness and safety of the YAG laser in the treatment of vitreous floaters. Shah et al. believed that Delaney used a low energy intensity when treating vitreous floaters with the YAG laser, only cutting rather than vaporizing the opacities, which resulted in poor therapeutic effects. A recent long-term follow-up study showed that the therapeutic effect of the YAG laser could be maintained for up to 18 months [8].

Although numerous studies have demonstrated the efficacy and safety of YAG laser vitreolysis, there remains controversy among some researchers regarding its widespread clinical use [9]. They argue that, as with any new treatment modality, moderate skepticism is warranted until further research demonstrates a favorable risk/benefit ratio. Additionally, Shah’s research found that objective improvement in patients’ vitreous floaters was 94%, while subjective improvement was only 53%, indicating a clear disconnect between objective and subjective responses that must be taken into account. On the efficacy front, the majority of current research does not rule out the placebo effect, as symptoms of vitreous opacities themselves may improve with gravity and neural adaptation. Complications of YAG laser are also worth paying attention to, such as lens damage, retinal hemorrhage, retinal vein occlusion, and postoperative high intraocular pressure [10–13]. To reduce intraoperative complications, YAG laser vitreolysis is recommended for patients with stable Weiss rings, with floaters located more than 2 mm away from the retina and more than 5 mm away from the lens [14].

To reduce intraoperative complications, current randomized controlled trials require inclusion criteria of patients with vitreous floaters lasting more than 6 months and completed posterior vitreous detachment [7, 15], which is not clinically practical. Many patients require intervention in the early stages of symptoms. There is a lack of research on the safety and efficacy of early YAG laser vitreolysis. Therefore, we undertook this clinical study to uncover that early YAG laser vitreolysis is both a safe and effective treatment option for vitreous floaters.

## Methods/design

The present prospective, randomized, controlled, double-blind, non-inferiority clinical trial aimed to evaluate the efficacy and safety of early YAG laser vitreolysis in treating symptomatic vitreous floaters. The clinical trial is presently being undertaken at Dongyang People’s Hospital, China. Ethical approval was obtained from the institutional ethics committee at the Dongyang People’s Hospital. Before enrollment, written informed consent was collected from the participants. The schedule for enrollment, intervention, data collection, and assessment was by the Standardized Protocol Items: Recommendations for Interventional Trials (SPIRIT) guidelines (see Fig. 1). The study flow schedule is depicted in Fig. 2. We followed the SPIRIT reporting guidelines during the drafting of this article [16].

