### Randomization and masking

In this study, a stratified randomization method will be used to allocate participants to two groups in a 1:1 ratio, using SPSS v26.0 (SPSS Inc, Chicago, IL, USA). The randomization process incorporates minimization and involves the consideration of three study variables for group stratification: sex (male/female), age (> 50/ ≤ 50 years), and crystal state (phakic eye/pseudophakic eye). A random allocation sequence will be created in advance and sealed in sequentially numbered opaque envelopes, allowing for randomization one at a time. Group allocation will be carried out by another researcher to ensure the randomization process is unbiased. All researchers involved in the study, including outcome assessors, statisticians, and data analysts, will be blinded to group assignment, but those providing the intervention will be informed as necessary. Before the trial, researchers will undergo comprehensive training in the randomization procedure and will be made aware of their responsibilities. The successful implementation and maintenance of the randomization and blinding methods will be validated to ensure the reliability and absence of bias in the trial results.

The investigator is strongly advised to uphold the blinding to the greatest extent possible. The actual allocation should not be revealed to the patient or any other study personnel, including site personnel, monitors, or project office staff. There should also be no written or verbal disclosure of the code in any of the patient-related documents associated with the study.

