### Sample size calculation

The sample size is determined a priori based on calculations assuming a modest improvement of 30% in symptoms in the YAG group compared to 10% in the sham group [7, 15]. This results in a sample of 66 patients with a standard deviation of 25%, an alpha level of 0.05, and a statistical power of 0.9. To account for a 5% rate of lost follow-up, it was decided to include 70 subjects in the study.

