### Statistics analysis

A comprehensive analysis is performed to delineate the demographic and clinical characteristics of the patient population. The normality of the variables is assessed using the Shapiro–Wilk test. The evaluated variables are depicted in tabular form, displaying both absolute and relative frequency distributions. Associations are examined utilizing either Pearson’s chi-square test or Fisher’s exact test, as warranted. The statistical significance of mean differences among quantitative variables is assessed through the paired and unpaired *t*-student tests. To assess variations across different time points within a group, the analysis of variance (ANOVA) with repeated measures is employed.

Continuous data are presented as mean ± standard deviation (SD), while categorical data are represented as counts (percentages). All analyses follow a two-tailed approach, with a significance level of 0.05. The statistical software package SPSS 17 (IBM Corporation, Armonk, NY) is employed for conducting data analysis, by established procedures.

In instances of data discontinuity, missing data will be handled by the “intention-to-treat” principle for conducting inferential statistical analysis. Missing data will be addressed through a dual strategy involving the last observation carried forward (LOCF) method and multiple imputation (MI). Additionally, sensitivity analyses will be conducted to evaluate the influence of various imputation methods on the study outcomes.

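### The trial is labelled non-inferiority, but it is sized and analysed to detect a difference from sham, and no margin is stated

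*Protocol article*

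**What the plan says.** The label appears once, in Methods/design: "The present prospective, randomized, controlled, double-blind, non-inferiority clinical trial aimed to evaluate the efficacy and safety of early YAG laser vitreolysis". The abstract calls the trial randomized, controlled and double-blind, without that term.

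The Sample size calculation section rests on a difference from sham, "assuming a modest improvement of 30% in symptoms in the YAG group compared to 10% in the sham group", and continues: "This results in a sample of 66 patients with a standard deviation of 25%, an alpha level of 0.05, and a statistical power of 0.9". It then adds: "To account for a 5% rate of lost follow-up, it was decided to include 70 subjects in the study".

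Under Statistics analysis, "The statistical significance of mean differences among quantitative variables is assessed through the paired and unpaired" t-tests, and "All analyses follow a two-tailed approach, with a significance level of 0.05". No margin is stated anywhere in the article.

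The comparator changes during follow-up. According to the abstract, "participants assigned to the delayed treatment group will receive a sham laser treatment and then undergo YAG laser vitreolysis 3 months later". The Primary outcome section lists two outcomes (a 0 to 10 symptom rating and the NEI VFQ-25) at 3, 6, 9 and 12 months, with a Bonferroni correction. The Background aims to show that early laser is safe and effective; the Discussion adds a comparison of early with delayed laser.

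**The concern.** A non-inferiority trial asks whether one treatment is worse than another by no more than a stated margin. A superiority trial asks whether the two differ. The hypotheses differ, and so does what a given result permits one to conclude. Here the declared framework is the first and the working parts belong to the second.

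Neither available contrast rescues the label:

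- **Up to month 3** the comparison is early laser against sham. Being no worse than sham in efficacy would not show that the laser works, which is the aim set out in the Background.
- **After month 3** both arms have had real laser. Non-inferiority of early to delayed laser would then be a sensible question, but the sample size was not calculated for it.

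At stake is the conclusion the trial may draw. Three of the four listed assessment times (6, 9 and 12 months) follow the delayed arm's real laser. A non-significant difference there would not establish non-inferiority, and the stated 90% power does not belong to a non-inferiority comparison.

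**Working it through.** **Inputs.** From Sample size calculation: improvement 30% against 10%, so a difference of 20 percentage points; SD 25 percentage points; alpha 0.05; power 0.90; 5% loss. From Statistics analysis: two-tailed testing. From Randomization and masking: "a stratified randomization method will be used to allocate participants to two groups in a 1:1 ratio". The non-inferiority margin is not given.

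**Step 1. Reproduce the plan's figure as two-sided superiority.**

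n per arm = 2 × [(1.96 + 1.2816) × 25 / 20]² = 32.8, rounded up to 33, so 66 in total.

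Allowing for loss: 66 / 0.95 = 69.5, rounded up to 70.

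Both figures match exactly. A t-based version gives 34 per arm (68). One-sided 0.05 gives 54, and treating 30% and 10% as proportions gives 164; neither of these two matches. The published calculation is therefore a two-sided comparison of means against sham.

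**Step 2. What 66 evaluable participants would give for non-inferiority.** The margins below are my assumptions. I also assume a true difference of zero, one-sided 0.025, and that the SD of 25 percentage points carries over to the contrast of interest.

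SE = 25 × √(2/33) = 6.15 percentage points.

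Power = Φ(margin / 6.15 − 1.96).

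| Assumed margin (percentage points of improvement) | margin / SE − 1.96 | Power |
|---|---|---|
| 5 | −1.15 | about 13% |
| 10 | −0.34 | about 37% |
| 15 | 0.48 | about 68% |
| 20 | 1.29 | about 90% |

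The 20-point row returns the planned power by construction: the same SD, alpha, power and formula give back the same difference. What it does show is that the planned number suits only a margin as large as the entire assumed benefit over sham (30 − 10 = 20).

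These are percentage points of improvement, the unit of the sample-size section. They are not points on the 0 to 10 rating or on the VFQ-25.

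**Step 3. Does relabelling as superiority fit the planned number?** At alpha 0.05, yes, from Step 1. The Bonferroni correction is a separate matter that exists under either label. The article does not give the number of comparisons. If it were two outcomes at one time point, each tested at 0.025, 90% power would need 78 evaluable participants. With 33 per arm, power would be Φ(20/6.15 − 2.24) = Φ(1.01), about 84% per outcome.

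**The case against.** The strongest reply is that this is one stray word. The term occurs once; the stated aims, sample size and tests all suit a difference design; and nothing in the article plans a non-inferiority conclusion. That is fair, and it makes the repair easy. It does not remove the contradiction, because the stray word sits in the sentence that defines the design.

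It could also be said that a margin belongs in an analysis plan that is not shown. But the article states its own sample-size basis, and that basis is superiority over sham. A margin held elsewhere would not turn this calculation into a non-inferiority one.

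A reader might infer more than the documents support:

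- **That two-sided testing at 0.05 is itself a fault.** It is not. A two-sided 95% confidence interval is equivalent to a one-sided 0.025 non-inferiority test. The gap is that differences are tested with no margin to set a bound against.
- **That the investigators intend to read a non-significant result as non-inferiority.** No section says so. It is a foreseeable risk of the label only.
- **That the trial has some particular low power, such as 37%.** Each such figure depends on an assumed margin, which is why a range is given.
- **That non-inferiority to sham is meaningless in every respect.** This holds for efficacy. For adverse events the question can be coherent, although the article does not say it was intended.

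**Conclusion.** The point holds in this form: the non-inferiority label in Methods/design contradicts the superiority basis of the sample size and the planned tests of differences, and no margin is stated. The contradiction needs no assumption, since 66 and 70 reproduce exactly as two-sided superiority over sham. As written, the design does not support a non-inferiority conclusion for early against delayed laser, because that contrast has neither a margin nor a sample-size basis.

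The illustrative power of 13% to 90% for margins of 5 to 20 percentage points rests on the assumed margins, a zero true difference and the borrowed SD. It shows the scale of the mismatch and is not a property of the plan. The correction should be made before analysis because it settles which conclusions are open to the trial.

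**What to change.** 1. Delete the term non-inferiority from Methods/design.
2. Declare the hypothesis as superiority of early YAG laser over sham at month 3, assessed before the second procedure, for the two outcomes in the Primary outcome section under the Bonferroni correction stated there.
3. Report early-versus-delayed differences at later visits as estimates with 95% confidence intervals.
4. State that no non-inferiority conclusion will be drawn from a non-significant test.

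**Cost.** This is a wording amendment. Under Data collection, management, and monitoring, it needs prior approval from the ethics committee, an entry in the trial registry and mention in the final report. What the registry now says about the framework is not known from the article. No extra patients or data are needed for this change; any power lost to the Bonferroni correction is there already. Trial status reports 32 enrolled at 19 September 2023 and recruitment extended to December 2024, so the article itself describes a trial still recruiting. What is given up is a claim the design could not support.

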**Fig. 1 Fig1:**
[figure not shown]
Standardized Protocol Items: Recommendations for Interventional Trials (SPIRIT)

**Fig. 2 Fig2:**
[figure not shown]
Flow of participants

### Participant eligibility

#### Inclusion criteria

Patients with a Weiss ring duration of less than 10 days and without additional eye complications will receive instructions to return to the hospital 1 month after the onset of symptoms. Subsequently, participants experiencing symptomatic floaters for precisely 1 month (28 to 32 days after the onset of symptoms) will be eligible for enrollment in the study. To be eligible for the study, the patient must rate their visual disturbance caused by floaters as at least 4 on a 0–10 scale, with 0 being no symptoms and 10 being debilitating symptoms. The symptomatic Weiss ring must be at least 2 mm from the retina and 5 mm from the posterior capsule of the crystalline lens, as measured on the B-scan. There is no minimum required distance from the intraocular lens for patients who have had cataract surgery (pseudophakic patients). The patient must be able to position themselves for the YAG laser procedure and accept the risks associated with the procedure, including but not limited to retinal detachment, intraocular hemorrhage, retinal damage, cataract formation, optic nerve damage, inflammation, and irreversible loss of vision. Additionally, the patient must be willing and able to comply with clinic visits and study-related procedures. If the patient has symptoms in both eyes, only one eye can be included in the study and randomized.

#### Exclusion criteria

The exclusion criteria are as follows: history of a retinal detachment, retinal tear, or uveitis in the study eye; history of macular edema, diabetic retinopathy, retinal vein occlusion, or aphakia in the study eye; history of glaucoma or high intraocular pressure, defined as having undergone glaucoma surgery in the eye being studied, or currently using two or more topical glaucoma medications in the eye being studied.

### Randomization and masking

In this study, a stratified randomization method will be used to allocate participants to two groups in a 1:1 ratio, using SPSS v26.0 (SPSS Inc, Chicago, IL, USA). The randomization process incorporates minimization and involves the consideration of three study variables for group stratification: sex (male/female), age (> 50/ ≤ 50 years), and crystal state (phakic eye/pseudophakic eye). A random allocation sequence will be created in advance and sealed in sequentially numbered opaque envelopes, allowing for randomization one at a time. Group allocation will be carried out by another researcher to ensure the randomization process is unbiased. All researchers involved in the study, including outcome assessors, statisticians, and data analysts, will be blinded to group assignment, but those providing the intervention will be informed as necessary. Before the trial, researchers will undergo comprehensive training in the randomization procedure and will be made aware of their responsibilities. The successful implementation and maintenance of the randomization and blinding methods will be validated to ensure the reliability and absence of bias in the trial results.

The investigator is strongly advised to uphold the blinding to the greatest extent possible. The actual allocation should not be revealed to the patient or any other study personnel, including site personnel, monitors, or project office staff. There should also be no written or verbal disclosure of the code in any of the patient-related documents associated with the study.

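### Allocation is described both as minimization and as a sequence sealed in envelopes in advance; minimization cannot be written out beforehand, so at least one stated element is not what the trial does

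*Protocol article*

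**What the plan says.** Everything on allocation stands in the Randomization and masking section of the protocol article, in consecutive sentences.

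- The method: "a stratified randomization method will be used to allocate participants to two groups in a 1:1 ratio, using SPSS v26.0".
- The balancing rule: "The randomization process incorporates minimization and involves the consideration of three study variables for group stratification". The three variables, each with two levels, are sex, age above 50 or not, and phakic or pseudophakic eye.
- Generation and concealment: "A random allocation sequence will be created in advance and sealed in sequentially numbered opaque envelopes, allowing for randomization one at a time".
- Who allocates: "Group allocation will be carried out by another researcher to ensure the randomization process is unbiased".

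Nothing links these statements. The section mentions no envelope set per stratum, no running tally of earlier allocations, no random element in the minimization, and no rule by which an envelope depends on the participant's characteristics.

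Two other places matter. The Statistics analysis section names t-tests, chi-square or Fisher tests and repeated-measures ANOVA; none of these is described as adjusted for the allocation factors. The Trial status section reports that recruitment began in November 2022 and that 32 participants were enrolled by 19 September 2023.

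**The concern.** Minimization and an allocation sequence prepared in advance are different mechanisms, and one participant's assignment cannot come from both. This is not a detail lost when a protocol is condensed into an article: the article positively states two mechanisms that exclude each other. A statistical analysis plan could not repair it either, because it cannot determine afterwards how participants were allocated.

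Three things depend on the answer.

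- **Balance.** The method decides which factors are balanced, and how closely.
- **Concealment.** It decides what keeps the next assignment hidden at a single centre where those giving the laser treatment know the assignments.
- **Analysis.** It decides which factors the primary comparison should account for.

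The same section also promises that the implementation of randomization will be validated. A procedure with two incompatible descriptions gives nothing definite to validate against.

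**Working it through.** **1. The plan's own figure.** The point rests on no stated figure, but the sample size was reproduced to see whether it is affected. Inputs from the Sample size calculation section: improvement of 30% against 10% (difference 0.20), SD 0.25, alpha 0.05, power 0.90; two-sided testing comes from the Statistics analysis section.

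n per arm = 2 × (1.960 + 1.282)² × (0.25 / 0.20)² = 32.8, so 33 per arm and 66 in total. With 5% loss, 66 / 0.95 = 69.5, so 70. The stated 66 and 70 reproduce. The allocation method does not enter this calculation.

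**2. The two mechanisms side by side.**

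| | Minimization | Sequence sealed in advance |
|---|---|---|
| What fixes assignment k | Factor levels of participant k, plus factors and arms of participants 1 to k−1 | Position k in the list |
| When it can be known | Only when participant k enrols | Before the first participant |
| Responds to sex, age, lens status | Yes | Only if there is a separate list per stratum |

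The information that minimization needs does not exist when the envelopes are filled. Conversely, an envelope filled beforehand cannot respond to the earlier participants' factors.

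**3. Readings that could be coherent.**

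- *Separate pre-made lists and envelopes per stratum.* Three binary factors give 2 × 2 × 2 = 8 strata, on average 70 / 8 = 8.75 participants each. This keeps stratification and envelope concealment, but it is not minimization.
- *Minimization run at enrolment by the independent researcher.* This keeps balance and can be concealed, but not by envelopes filled beforehand.
- *One pre-made list that ignores the factors.* This keeps the envelopes but delivers neither stratification nor minimization.

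Under each reading at least one stated element is untrue.

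**4. Illustration of balance.** The article gives no factor prevalences, block size or minimization probability, so all of these are assumptions. A simulation used 70 participants, three independent binary factors and 2,000 runs per method. Ranges cover assumed prevalences of 35/15/15% and 50/50/50%.

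| Method | Mean largest between-arm difference within any factor level | Chance that it is 6 or more |
|---|---|---|
| Minimization, probability 0.8 | 2.1 to 2.2 | about 1% |
| Pre-made list per stratum, blocks of 4 | 2.5 to 2.7 | about 1% |
| One pre-made list, blocks of 4, factors ignored | 4.8 to 5.8 | 32% to 51% |
| One simple randomization list | 8.6 to 8.9 | 75% to 84% |

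The first two methods balance about equally well.

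**5. Worst case for lens status.** Assume one unstratified 35/35 list, so that the number of pseudophakic eyes in one arm is hypergeometric (70 participants, 35 per arm). The article gives no number of pseudophakic participants, so three assumed values are shown.

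- 7 pseudophakic: a difference of 6 or more can only be 7:0, chance 0.01.
- 14 pseudophakic: 9:5 or worse, 0.371; 10:4 or worse, 0.133.
- 21 pseudophakic: the difference must be odd, so 6 or more means 14:7 or worse, 0.117.

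**The case against.** The strongest reply is that this is loose terminology. The section opens by calling the method stratified and never says that there is one envelope series. Envelopes numbered within each stratum are an ordinary way to carry out stratified randomization, and an article would commonly leave that to the full protocol. On that reading balance and concealment are both delivered, and only the word *minimization* is wrong. It can also be argued that the process merely incorporates minimization, with a pre-generated random list serving as its tie-break or random element.

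Much of this stands. A reader might infer that stratification is absent, that concealment fails, or that the next assignment can be predicted. The article supports none of these. The first requires a single envelope series, which it does not state. The second overlooks that minimization run by an independent person can be concealed. The third treats silence about a random element as proof that there is none, although the section has another researcher allocate and forbids disclosure of assignments. The probabilities for a single list describe a worst case that conflicts with the stated stratification, and they rest on assumed counts. Even there the practical effect can be small: with 14 pseudophakic participants split 9:5, the phakic eyes, in which damage to the natural lens can occur, number 26 against 30.

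The reply does not remove the contradiction. Envelope sets per stratum are not minimization. A tie-break list is not the allocation sequence that the article says is sealed in the envelopes. The article states neither reading, and each requires withdrawing something that it does state.

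**Conclusion.** The allocation rule cannot be followed as written. This is a stated contradiction within one section, and it follows from what minimization is, without any numerical assumption. It should be corrected while participants are still being allocated.

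Its consequence is open. Balance and concealment may both be intact, or one of them may be weaker than described, depending on what was done. The simulated imbalances and the hypergeometric probabilities only bound the possibilities under assumed prevalences and do not describe this trial. Neither bias nor an inflated type I error is shown, and the sample size of 70 does not change.

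**What to change.** 1. State which method allocated the 32 participants enrolled by 19 September 2023, and report it with the results.
2. Use one coherent method for the rest (70 − 32 = 38 at that date), and describe only that method:
   - (a) stratified permuted blocks with a separate concealed envelope series for each of the 8 strata, deleting *minimization*; or
   - (b) minimization on the three factors with a random element, run at enrolment by the independent allocator, deleting the advance sequence and the envelopes.
3. Under either method, adjust the primary comparison for sex, age group and lens status. The article names only unadjusted tests, and these factors are already collected. If an analysis plan that is not shown already provides for this, a cross-reference is enough.

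The cost is a wording amendment, submitted to the ethics committee and recorded in the registry as the article requires for any modification, plus re-preparing the unused envelopes or setting up a simple allocation program. No extra participants, visits or measurements are needed.
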